#### Safety outcomes

The safety outcomes will include any AEs and clinically meaningful changes in vital signs or laboratory examination during the trial, including blood routine (RBC, WBC, HGB, PLT), urine routine (WBC, RBC, urine glucose), stool routine (qualitative + occult blood), liver function (ALT, AST, GGT, TBIL, ALP), renal function (BUN, Cr, UA, eGFR), myocardial enzyme spectrum (CK, CK-MB, LDH), and ECG. These evaluations will be performed before enrollment and after 3, 6-month treatment and 12-month follow-up respectively.

### Quality control and data monitoring

First, all investigators will receive unified training according to the investigator’s instruction manual before the start of the study. The principal investigator will convene monthly meetings to discuss and resolve the problems in the trial (including subject recruitment, withdrawal, AEs, data collection and protocol modifications). Additionally, investigators shall obtain ICF from the trial subjects.

Secondly, CRF is filled by investigators and CRC according to the investigator's brochure in every clinical research sub-center. Subjects with basic diseases, including stroke and coronary heart disease, who have been taking medication for a long time and are stable, should continue to participate in the trial, however, combined drugs must be filled in the CRF. Those with unstable basic diseases will be excluded from the study. Subjects experiencing allergies or other side-effects or intolerance during medication or aggravated due to basic diseases and those unwilling to continue to participate for some reasons such as the COVID-19 pandemic should record their reasons for withdrawal in the CRF. In case of an emergency, and there is a need to uncover the blinding codes, the date and reason shall be filled in CRF.

Thirdly, regarding data monitoring and management, Clinical research associate (CRA) from Hinye Pharmaceutical Co., Ltd. will check the CRF data monthly. EpiData Entry will be performed by the statistical professionals of the Drug Clinical Evaluation Research Center of Central South University. Two personnel will enter the data into the database. The statisticians will check the original data and promptly issue a query to the investigator after identifying problems, then provide data to the recorder for modification. Data management and statistics will be performed after correction.

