The onset of HT-CSVD is difficult to be diagnosed and can easily be ignored by clinicians and patients. Without effective intervention, HT-CSVD gradually progresses to cerebral hemorrhage, cerebral infarction, and other cerebral macrovascular diseases. Therefore, early intervention and treatment may be of great significance. At present, specific treatment for HT-CSVD is lacking. The current therapeutic strategies include symptomatic treatment and controlling risk factors, i.e., reducing BP, antiplatelet therapy, thrombolysis, and statin therapy (Cannistraro et al., 2019). Nevertheless, these therapies have contraindications and complications. For example, although statin therapy has demonstrated a significant beneficial effect in patients with ischemic stroke, patients receiving high-dose atorvastatin exhibit an increased risk of intracerebral hemorrhage (ICH) recurrence, specifically in patients with CSVD (Amarenco et al., 2009; Cannistraro et al., 2019). Therefore, there is an urgent need to identify new, safe and effective treatment strategies for HT-CSVD.

Traditional Chinese medicine (TCM), with the advantages of early conditioning and multi-target, is responsible for the prevention and treatment of HT-CSVD (Lin et al., 2021; Li et al., 2020; Zhou et al., 2022). Based on TCM theory, Qi deficiency and blood stasis (QDBS) is the major mechanism of HT-CSVD (Lin et al., 2021) and cerebral ischemia or ischemic/reperfusion injury. Notably, QDBS is a complex pathological system accompanied by oxygen radical accumulation, inflammation, vascular endothelial damage, and viscera injury, which in turn further promotes the development of QDBS (Bi et al., 2019; Zhang et al., 2020; Liu et al., 2021). According to TCM theory, Qi pushes the blood to circulate in the channels and can produce blood. Qi deficiency reduces blood production and cannot nourish the meridians, hence a lack of nutrition in the brain tissue. As a result, the body becomes prone to cognitive impairment and memory loss. Moreover, Qi deficiency hinders blood circulation; hence blood stasis stagnates in the veins or circulates outside the veins. The above changes in blood circulation induce cerebral vascular embolisms or CMB (Wang et al., 2021), gradually causing HT-CSVD.

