### Statistical analysis

All statistical analyses will be performed using the SPSS 22.0 statistical software. Descriptive statistics will be used for baseline characteristics data. Quantitative variables (numerical variables) will be analyzed by the normality test (such as *Shapiro-Wilk*), and normal distribution numerical variables will be compared using two independent *t*-tests or analysis of variance (*ANOVA*) and other potential confounding variables (such as multicenter characteristics) as covariates. Numerical variables will be summarized with mean ± SD. Non-parametric tests (*Wilcoxon rank-sum* test, *Kruskal–Wallis* test) and M (P_25_, P_75_) will be used to describe the non-normal distribution. Qualitative variables (categorical variables) are represented by the number of cases and the composition ratio; comparison among groups will be performed using the chi-square test or Fish precision probability. Non-parametric test or analysis of covariance will be used to compare the difference in therapeutic indexes. The efficacy analysis adopts the intention to treat (ITT) analysis and the per-protocol set (PPS). Subgroup analysis will be performed regardless of whether the treatment significant effect the main outcome. Safety analysis will be performed by analyzing the incidence of intergroup AEs and abnormal laboratory examination results before and after treatment.

The full analysis set (FAS) will be conducted for the therapeutic indexes of all subjects included in the study. Statistical analysis in accordance with PPS will be conducted for the therapeutic indexes of subjects completing the drug intervention for 6 months. FAS uses the last-observed-carried-forward method (LOCF) to adjust the missing data and complete ITT analysis. The safety analysis will be performed using the safety analysis set (SS). All statistical tests will be two-sided. *p* ≤ 0.1 means there is a statistical difference, *p* ≤ 0.05 represents a significant statistical difference.

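### The withdrawal rules do not separate stopping capsules from leaving the study, so subjects who worsen clinically (for example a new stroke) may lack a month-6 MRI and be analysed as unchanged

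*Protocol article*

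**What the plan says.** Three parts of the protocol article bear on this.

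- **Quality control and data monitoring.** Stable subjects stay: "Subjects with basic diseases, including stroke and coronary heart disease, who have been taking medication for a long time and are stable, should continue". Then: "Those with unstable basic diseases will be excluded from the study". The next sentence concerns events on treatment. It covers "Subjects experiencing allergies or other side-effects or intolerance during medication or aggravated due to basic diseases", together with subjects unwilling to go on, and asks that their reason for withdrawal be entered in the CRF. It says nothing about assessments after withdrawal.
- **Assessment data, Primary outcome and Secondary outcomes.** Fazekas score, dVRS grade and the numbers of lacunar infarcts (LI) and microbleeds come from MRI before enrolment and after 6 months of treatment. No MRI is planned in between.
- **Statistical analysis.** "The full analysis set (FAS) will be conducted for the therapeutic indexes of all subjects included in the study". The per-protocol set (PPS) is subjects who complete 6 months of drug. For missing values, "FAS uses the last-observed-carried-forward method (LOCF) to adjust the missing data and complete ITT analysis".

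The disease background also matters. The CSVD diagnostic criteria describe CSVD as characterised mainly by stroke, including small deep infarction, and list acute LI among its imaging features. The Introduction says that, without effective intervention, "HT-CSVD gradually progresses to cerebral hemorrhage, cerebral infarction, and other cerebral macrovascular diseases".

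**The concern.** Stroke appears in two roles. In the quality control section it is a basic disease whose instability leads to exclusion and whose aggravation is a reason for withdrawal. In the diagnostic criteria and Introduction, small deep infarction is a manifestation of the disease under study, and cerebral infarction a stage of its progression. A site could therefore reasonably handle an on-study lacunar stroke, at least in a subject with a previous stroke, as an aggravated basic disease and withdraw the subject.

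Because stopping capsules and leaving the study are not distinguished, the month-6 MRI may be lost with the capsules. The subjects lost would then include some of those most likely to have a new lacune or a higher Fazekas score. If the capsules slow progression, more placebo subjects leave for worsening and the observed effect shrinks. If the capsules cause intolerance, more active-arm subjects leave and the direction of bias is unknown. No analysis method recovers an MRI that was never taken, so this is a question of follow-up as well as of imputation.

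**Working it through.** **1. What happens to a withdrawn subject.** Take a randomised subject withdrawn at month 4 after a symptomatic lacunar stroke (an illustrative case, not one in the article).

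- Month-6 MRI: none is described after withdrawal.
- PPS: left out, because 6 months of drug were not completed.
- Full analysis set (FAS): the only earlier MRI is baseline, so last observation carried forward (LOCF) enters the baseline Fazekas score, dVRS grade and LI count. The change is 0 and the new infarct is not counted in LI.
- One ambiguity remains. If exclusion from the study also means no longer being among the subjects included in it, the subject is not in the FAS either. The text does not settle this.

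**2. The plan's own figures.** From the sample size section: SDs 1.26 and 1.3, difference 0.5, z-values 1.65 and 0.85, dropout 20%.

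- Pooled SD = √((1.26² + 1.3²)/2) = 1.280.
- n per group = (1.65 + 0.85)² × 2 × 1.280² / 0.5² = 81.94, printed as 81.
- 81 × 1.2 = 97.2 per group; 4 × 97 = 388, as stated.

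This gives 97 per arm within a stratum and 194 per arm with strata pooled. The sample size is not in dispute here; these figures only supply the scale for steps 4 and 5.

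**3. How many subjects.** The Abstract gives a 14% one-year stroke recurrence.

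- Six-month risk at a constant rate: 1 − (1 − 0.14)^0.5 = 0.073.
- 388 × 0.073 = 28.
- With an assumed floor of 1%: 388 × 0.01 = 4.

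The 28 is a ceiling for stroke-driven withdrawal. It applies a recurrence rate to everyone, including the stratum without brain-damage symptoms, and assumes that every such subject is withdrawn. The article gives no rate for withdrawal through intolerance or other basic diseases.

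**4. Shift in the FAS difference.** Under LOCF a withdrawn subject's true change g is replaced by 0. If g is the same in both arms, the between-arm difference moves by g × (difference in withdrawal proportion). Assume g = 1 to 2 Fazekas points and a 2 to 4 percentage-point excess of withdrawals on placebo:

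- smallest: 1 × 0.02 = 0.02, or 4% of 0.5;
- largest: 2 × 0.04 = 0.08, or 16% of 0.5.

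**5. Effect on power.** Let w be the share of the planned 0.5-point difference lost in this way, with SD unchanged. Power at two-sided alpha 0.10 = Φ(0.5(1 − w) / (1.280 × √(2/n)) − 1.645). For n = 97 and w = 0: 0.5/0.1838 = 2.720, and Φ(2.720 − 1.645) = 85.9%.

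| w | Difference | 97 per arm | 194 per arm |
|---|---|---|---|
| 0 | 0.50 | 85.9% | 98.6% |
| 10% | 0.45 | 78.9% | 96.5% |
| 16% | 0.42 | about 74% | about 94% |
| 20% | 0.40 | 70.2% | 92.4% |
| 40% | 0.30 | 49.5% | 74.6% |

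No value of w comes from the documents. The table shows sensitivity and is not a forecast.

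**The case against.** Several points on the other side are good, and they limit the finding.

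- **The FAS exists.** A reader might infer that the intention-to-treat population cannot be formed. The documents do not support that. The FAS is defined on all included subjects, separately from the PPS, and LOCF is there to complete it. The weakness is that baseline values stand in for outcomes.
- **No rule removes a subject for CSVD progression.** A reader might infer that progressing patients as a group leave before the month-6 MRI. CSVD is never called a basic disease; stroke and coronary disease are named as long-treated comorbidities. Progression on Fazekas or dVRS becomes visible only at month 6 and cannot trigger earlier removal. Only clinically evident worsening could.
- **The exclusion sentence may be an eligibility rule.** That is possible. Against it, none of the eleven listed exclusion criteria is worded as unstable basic disease, and the sentence sits beside one about continuing in the trial. Even on the eligibility reading, the following sentence on withdrawal during medication remains.
- **Symptomatic infarcts are not lost altogether.** Adverse events are recorded with onset, cause and treatment and compared between groups. The event would be missing from the LI count, not from the trial record.
- **An article may leave post-withdrawal follow-up to the full protocol.** This holds for the missing detail, but not for the gap that the stated rules create: withdrawal on worsening, MRI at two times only, and LOCF.
- **The magnitude is mostly assumed.** This stands. Even the largest shift in step 4 leaves power at about 94% with strata pooled.

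**Conclusion.** The concern holds in a limited form. The quality control and statistical analysis sections do not fit together. The first leaves open when exclusion for unstable disease applies and merges stopping capsules with leaving the study. The second promises an analysis of all included subjects but, for MRI outcomes, can offer only baseline values for those who leave. Because stroke is both a named basic disease and a manifestation of the condition treated, some of this loss can depend on outcome and on treatment, and the Fazekas, dVRS and LI comparisons can be biased.

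The size cannot be derived from the documents. The ceiling of 28 subjects rests on a constant rate and on applying recurrence to all 388. The shift of 0.02 to 0.08 points rests on assumed progression and an assumed arm imbalance. The point deserves correction, but nothing here shows that it invalidates the trial.

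**What to change.** 1. Reconcile the quality control and statistical analysis sections: state whether exclusion for unstable basic disease applies before or after randomisation, and whether anyone excluded or withdrawn afterwards remains in the FAS. Which timing is right is for the sponsor to decide.
2. State that stopping capsules is not leaving the study. Every randomised subject who has not withdrawn consent keeps the scheduled month-3 and month-6 assessments, including the month-6 MRI, and is analysed as randomised.
3. Where visits have already passed, keep all randomised subjects in the FAS, report withdrawals by arm and reason, and add a sensitivity analysis for outcome-related withdrawal. This may be the main route, since Table 1 gives recruitment as completed and the Discussion expected the trial to finish in December 2022.

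The criteria for stopping treatment are left unchanged.

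Cost: protocol wording, a site instruction and one further analysis. The visits and MRI are already scheduled for every subject. The downside is some effort to bring back subjects who are off drug, and an effect estimate that includes off-drug time.

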### Sample size calculation

At present, there is no clinical research report on TCM treatment for WML of CSVD. According to our previous case-control study, Fazekas grades of WML are an independent risk predictor of stroke (*p* < 0.01). With WML levels of 0–3 increasing step by step, delayed memory, spatial, and executive dysfunction appear at WML level 2, specifically at WML level 3. The mean ± standard deviation (SD) of Fazekas scores of HT-CSVD patients was 2.29 ± 1.26 (Zhou et al., 2022). After 6 months of NTF treatment, the mean ± SD of Fazekas scores is 2.29 ± 1.26 for the intervention group and 2.8 ± 1.3 for the control group (since CSVD is a progressive brain disease, we speculate that Fazekas grades of control groups will increase at least 0.5 points after 6 months without intervention). Considering α 10% significance level, the Z-value is based on the Z-value table for two-tailed distribution of 1.65. The β-value is determined at 0.20, and the Z-value is based on the Z-value table for a one-tailed distribution of 0.85. When the dropout rate is 20%, the sample size is calculated using an estimation formula for comparison of the mean values of two independent samples as follow:
$$N=\frac{{\left(Z_{\alpha /2}+Z_{\beta }\right)}^{2}*{\left(1+1/k\right)\;\sigma }^{2}}{\delta^{2}}=\frac{{\left(1.65+0.85\right)}^{2}*2*\left({1.26^{2}+1.3}^{2}\right)/2}{0.5^{2}}=81$$

Where N is the sample size of each group; Z_a_ is the table of Z-value for two-tailed distribution; Z_β_ is the table of Z-value for one-tailed distribution; σ is the standard deviation; δ represents the difference. The number of cases that may drop out is added; thus, 388 subjects will be required.

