### Randomization

This study uses a stratified block randomization approach. The participants were grouped into HT-CSVD with clinical manifestations of brain damage and HT-CSVD without clinical manifestation of brain damage based on the presence or absence of clinical manifestations of brain damage. An appropriate block length was selected (the size of block is 4) and random assignment was conducted using the SAS 9.4 statistical software (SAS Institute, North Carolina, United States) developed by statisticians from the Drug Clinical Evaluation Research Center of Central South University. 194 random sequences were generated for each group, that is, the randomized coding table with No. 001-194 was developed. The participants of each group were randomly divided into the intervention group and the control/placebo group at an allocation ratio of 1:1. Randomized codes were used as the drug numbers which were kept in an opaque sealed envelope and taken to Hinye Pharmaceutical Co., Ltd. (Changsha Hunan, China) for unified drug label production. The identification code of each subject was similar to the drug number.

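### The 388 subjects do not cover the stated 20% dropout on the plan's printed inputs; 80% power per stratum at alpha 0.10 holds only up to about 15.5% dropout

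*Protocol article*

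**What the plan says.** All references are to the protocol article.

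- **Sample size calculation**, error rates: "Considering α 10% significance level", with "the Z-value table for two-tailed distribution of 1.65"; "The β-value is determined at 0.20", with a z-value of 0.85.
- **Sample size calculation**, effect: expected six-month Fazekas scores of 2.29 (SD 1.26) on treatment and 2.8 (SD 1.3) on control. The formula uses a difference of 0.5 and prints 81, defined as the size of each group.
- **Sample size calculation**, dropout: "When the dropout rate is 20%, the sample size is calculated using an estimation formula". The section ends: "The number of cases that may drop out is added; thus, 388 subjects will be required". It does not show how the dropouts were added.
- **Randomization**: "194 random sequences were generated for each group", where the groups are the two strata (with and without clinical manifestations of brain damage), each split 1:1. That is 97 per arm per stratum and 2 x 194 = 388.
- **Statistical analysis**: "All statistical tests will be two-sided", and "p* ≤ 0.1 means there is a statistical difference, *p* ≤ 0.05 represents a significant statistical difference".

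**The concern.** A dropout allowance should leave the required number of evaluable subjects after the assumed loss. Here the required number is 81 or 82 per group, and 97 per group less 20% leaves fewer than that. The stated allowance and the stated total therefore disagree.

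At stake is how a result within one stratum is read. The total follows only if four groups are each given the computed size, so each stratum appears to be sized to stand alone. A null result in one stratum would be judged against 80% power, which the design does not quite have at the assumed dropout.

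A separate matter is which threshold that 80% refers to. The size is set at alpha 0.10, while the analysis section gives its stronger label to p ≤ 0.05. The protocol gives no power for that second threshold.

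**Working it through.** **Inputs (Sample size calculation):** z-values 1.65 and 0.85; SDs 1.26 and 1.3; difference 0.5; dropout 20%. The common SD is √[(1.26² + 1.3²)/2] = √1.6388 = 1.280.

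**1. The printed formula.** (1.65 + 0.85)² x (1.26² + 1.3²) / 0.5² = 6.25 x 3.2776 / 0.25 = 81.94, which rounds up to 82; the article prints 81. With unrounded z-values (1.645 and 0.842) the result is 81.06, again 82 when rounded up. The cut to 81 has no practical effect: 81 per group has 79.98% power by the normal approximation.

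**2. Reproducing 388.** 81 x 1.2 = 97.2, cut to 97; 4 x 97 = 388. The multiplication by 1.2 is inferred, since the article does not show the step, but it gives the total exactly, and 194 codes per stratum at 1:1 confirm 97 per arm.

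**3. Does 97 cover 20% dropout?** 97 x 0.8 = 77.6, below both 81 and 82. This does not depend on how 97 was reached. The largest dropout that leaves 82 is 1 − 82/97 = 15.5%; for 81 it is 1 − 81/97 = 16.5%.

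**4. Totals with division by 0.8:**

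| Evaluable per group | Basis | Per group after division | Total (x 4) |
|---|---|---|---|
| 82 | difference 0.5 | 102.5 → 103 | 412 |
| 81 | as printed | 101.25 → 102 | 408 |
| 79 | difference 0.51, rounded z (78.76) | 98.75 → 99 | 396 |
| 78 | difference 0.51, exact z (77.91) | 97.5 → 98 | 392 |

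The shortfall is 24 subjects on the formula's own difference (412 − 388). It is 4 to 8 if the difference between the stated means, 2.8 − 2.29 = 0.51, is used.

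**5. Power** (normal approximation, difference 0.5, SD 1.280):

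| Evaluable per arm | Situation | Alpha 0.10 | Alpha 0.05 |
|---|---|---|---|
| 77.6 | one stratum, 20% dropout | 78.5% | 68.2% |
| 82 | one stratum, dropout correctly allowed for | 80.4% | 70.6% |
| 97 | one stratum, no dropout | 85.9% | 77.6% |
| 155.2 | both strata pooled, 20% dropout | 96.4% | 93.1% |

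The noncentral t gives 78.2% and 67.6% in the first row. With a difference of 0.51 and 77.6 per arm, the normal approximation gives 79.9% and 69.9%.

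**6. Separating the two effects.** At alpha 0.10 the dropout step costs about 2 points (80.4% to 78.5%). At 0.05 it costs a similar amount (70.6% to 68.2%). The remaining 10 points or so come from the change of alpha alone.

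**The case against.** The strongest case against the point is that the slip is nearly harmless. At the alpha the plan chose, power falls to about 78%, and with the 0.51 difference between the stated means it is 79.9%. Table 1 lists recruitment as completed, and the Discussion already calls the trial exploratory and concedes that its size may be too small. All of this stands. It limits the severity, but it does not make the dropout statement correct on the inputs that the formula uses.

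It can also be said that 77.6 counts completers only, because the full analysis set keeps dropouts through last observation carried forward. That is true, but it does not restore the power. Brain MRI is done only before enrolment and after 6 months, so a dropout can only have the baseline score carried forward. If treated scores stay level and control scores rise by 0.5 as the plan expects, equal 20% dropout reduces the difference to 0.8 x 0.5 = 0.40. With all 97 per arm and an unchanged SD (an assumption), the standard error is 1.280 x √(2/97) = 0.184 and the ratio is 2.18. Power is then about 70% at alpha 0.10 and 58% at 0.05.

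A reader might go further and infer that the trial has 68% power where the plan promised 80%. The documents do not support that. The 80% is set at alpha 10%, which agrees with the p ≤ 0.1 threshold in the analysis section, and 80% at 0.05 is never claimed. The 68% comes almost entirely from moving to 0.05, since correct inflation would give only about 71% there. It also applies within one stratum only.

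**Conclusion.** The point holds as an inconsistency between the stated dropout rate and the stated total. On the printed inputs, 388 leaves 77.6 evaluable per group where 82 are needed. The total would be 412 on those inputs, 408 from the printed 81, and 392 to 396 with the difference of 0.51. Power per stratum at alpha 0.10 is about 78% at 20% dropout. That is a minor-to-moderate fault.

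The power at 0.05 is a separate question of reporting and is not a consequence of the dropout step: about 68% within a stratum and about 93% pooled. The article does not say which comparison carries the main conclusion, so neither figure can be taken as the power of the trial.

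These figures assume the plan's means and SDs, equal dropout in all groups and an analysis of completers. The pooled figures also assume the same effect in both strata, although the strata receive different doses.

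**What to change.** Keep 388 and correct the text in Sample size calculation:

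- Give the requirement as 82 evaluable per group and show that 388 is 97 in each of four groups.
- State either that 80% power per stratum at two-sided alpha 0.10 holds for dropout up to about 15.5%, or that it is about 78% at 20% dropout.
- Use one difference, 0.5 or 0.51, in both the text and the formula.

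As a separate change, name the comparison (per stratum or pooled over strata) and the alpha on which the conclusion will rest, and quote the power for that pair. If the alpha is 0.05, the figures at 20% dropout are about 68% per stratum and about 93% pooled.

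The cost is wording only. No patients are added, and the stated per-stratum power becomes slightly less favourable.
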